## Discussion

In this paper, we describe the study design of a randomized controlled trial aimed at evaluating the effects of an internet-based, guided self-help intervention for depressive symptoms in glioma patients. This study is innovative in two ways: 1) as of yet, there is no evidence from RCTs for the effectiveness of psychotherapy in glioma patients with depressive symptoms; and 2) to our knowledge, providing psychosocial care through the internet has not been explored in the depressed glioma patient population until now.

We expect the external validity of this study to be high, as we employ only few exclusion criteria. Any adult WHO grade II, III or IV glioma patient at any disease stage with mild depressive symptoms is invited to participate in the trial to try and relief these symptoms. Furthermore, as the intervention is administered through the internet and patient inclusion is organized nation-wide, we should be able to reach a large group of potential participants. Using the internet also evidently has its downsides. For certain patients, such as those unaccustomed to using the computer in their everyday lives or those with more severe cognitive impairment, using the internet may prove more difficult and could possibly result in non-participation or dropout of the study. We aim to construct the website in a very straightforward and easy-to-use way, in order to minimize this possibly negative effect. In addition, both interventions using the internet and self-help interventions are prone to high dropout rates [49], suggesting that this problem could occur in our trial as well. Therefore we present the online questionnaires separately from the intervention website, and email reminders are sent for both the assessments and the course assignments separately. Moreover, if participants do not respond to these reminders, we try and contact them through telephone instead. This should strengthen the relationship between the participants and the researchers substantially, thereby possibly improving patient participation throughout the trial [50].

Our frequent follow-up assessments, up until 12 months after the guided self-help course, enable evaluation of both short- and long-term effects of the intervention. However, frequent evaluation of mental well-being through self-reported questionnaires may also lead to patients’ increased awareness of their depressive symptoms. To minimize this possible effect we keep track of the patients’ suicidal ideation and depressive symptoms throughout follow-up and we will contact both the participant and their general practitioner in case symptoms worsen significantly.

Due to its nationwide design, our study could raise awareness of depressive symptoms among both physicians and patients. Whereas this is favorable for patients, it may lead to a risk of contamination in this randomized controlled trial, as more psychological help may be offered outside of the intervention offered in our study. However, the TIC-P assessment records all contact with health-care professionals, so with adequate power we will be able to correct for this in the analyses.

In conclusion, we currently present the design of our study aimed at improving symptoms of depression in glioma patients using a brief internet-based guided self-help intervention based on the principles of PST. This can provide methodological clarity and can aid and encourage further research efforts to improve mood and HRQOL in glioma patients. Our randomized controlled trial is expected to contribute substantially to the existing literature as there is a hiatus in studies evaluating the effectiveness of different treatments for depression, as well as interventions delivered by means of the internet in this patient population. Furthermore, implementation in clinical practice should be relatively easy to accomplish if our intervention proves to be effective, as it only requires minimal involvement of health care professionals. Currently, this trial is in the recruitment phase.

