### Randomization

Glioma patients are randomly assigned to either the intervention group or the waiting list control group after completion of the baseline assessment (T0). An adaptive simple randomization technique is employed to minimize the chance of imbalanced group sizes.

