### Intervention

The internet-based guided self-help intervention is based on the principles of problem solving therapy. The original intervention, ‘Everything under control’ (“*Alles onder controle*”) has been shown to have significant positive effects on depression, anxiety and stress/burnout in a randomized controlled trial with 215 adults from the general population [39]. With small changes, this online intervention is adapted for use by glioma patients and patients with haematological malignancies. Modifications concern additional information about the specific diseases and their treatment, and the psychological impact on everyday life. Examples of participants’ assignments are made disease-specific.

The intervention consists of 5 modules with text and exercises. Patients are asked to complete one module a week and spend a minimum of two hours a week on their exercises. During the intervention, patients describe what they feel is important in their lives, make a list of their problems and concerns, and divide these into three categories: 1) unimportant problems (problems that are not related to what is important in their life), 2) important and solvable, and 3) important but unsolvable. For each of these problems the patient makes a plan on how to cope with this, guided by methods explained in the modules. The participants receive feedback on the exercises from a personal coach within three working days after completion of the assignment. The coach is not a therapist, but only supports the patient in working through the intervention. Participants can always contact their coach for additional support through the website. The coaching is provided by one of the researchers ([name]), by trained and supervised students in the final phase of a Master’s program in Psychology or by specialists from Prezens. In collaboration with the VU University medical center, Prezens provides psychological care and support.

The glioma patients in the waiting list control group are offered the same intervention after completion of the 12 weeks follow-up (T2).

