### Statistical analyses

Appropriate parametric and non-parametric statistical tests will be employed to examine differences between the groups in terms of all relevant demographic and clinical variables at baseline. Missing observations at follow-up will be imputed using the multiple imputation procedure [48]. Following the CONSORT guidelines, the intention-to-treat principle will be applied. All randomized participants will be included in the analyses, regardless of how many treatment modules or sessions they complete. Within-group and between-group differences (e.g., patients with or without epileptic seizures, pain, neurological deficits, or self-reported cognitive deficits) in dependent variable scores will be analyzed using both univariate and multivariate statistical techniques. For between-group statistical comparisons, sociodemographic variables (age, gender, and education) will be used as covariates, where necessary. The effects of the interventions will be tested by means of Helmert contrasts. Relative improvements in depressive symptoms (CES-D score) in the experimental group compared with pre-treatment assessment as well as both control groups will be calculated using Cohen’s d. If the primary outcome measure is non-normally distributed, the test and the 95% confidence intervals will be based on robust standard errors and/or on non-parametric bootstrap techniques. This will help to correctly ascertain the relative effectiveness of the treatment over the control conditions.

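### Correcting the treatment comparison for outside psychological help recorded after randomisation can bias it, and adequate power does not prevent this

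*Protocol article*

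**What the plan says.** The Discussion of the protocol article warns that the study may raise awareness of depression among physicians and patients and that "it may lead to a risk of contamination in this randomized controlled trial, as more psychological help may be offered outside of the intervention". Its answer is that "the TIC-P assessment records all contact with health-care professionals, so with adequate power we will be able to correct for this in the analyses". Adequate power is the only condition attached. No method is named, and nothing limits the correction to a sensitivity analysis.

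Four other places bear on this:

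- **Randomization:** allocation comes "after completion of the baseline assessment (T0"), so care recorded at later assessments is post-randomisation.
- **Discussion, on monitoring of mood:** "we will contact both the participant and their general practitioner in case symptoms worsen significantly".
- **Intervention:** "The glioma patients in the waiting list control group are offered the same intervention after completion of the 12 weeks follow-up (T2").
- **Statistical analyses:** "Following the CONSORT guidelines, the intention-to-treat principle will be applied". Age, gender and education are the only covariates named, and outside care is not among them.

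The TIC-P also supplies the cost data, which the article lists among the secondary outcomes.

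**The concern.** A baseline covariate cannot be affected by the allocated arm. Care used during follow-up can be. It can also respond to the course of depression, which is the primary outcome. If arm (directly or through mood) and mood both influence who gets help, patients with equal help in the two arms are no longer comparable. A help indicator in the model then partly stands in for worse mood, and the arm coefficient moves for reasons unrelated to the course.

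The justification given is a matter of precision. Power determines how accurately the adjusted coefficient is estimated, but not whether it estimates the right quantity. A reader who accepts the sentence could take the corrected figure as the uncontaminated effect of the course, when it may lie further from that effect than the uncorrected figure does.

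**Working it through.** **Is the variable affected by arm or outcome?** Set side by side, the passages give three links.

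1. Time order: randomisation follows T0, and the feared help is help obtained during the trial.
2. Mood to help: significant worsening triggers contact with the general practitioner, a route to outside care built into the trial.
3. Arm to help: controls get the course only after T2, so they have more reason to look elsewhere in the first 12 weeks. This link is an inference; the article's own mechanism, greater awareness, is not tied to an arm.

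**How far does adjustment move the estimate?** For least squares of outcome on arm and a help indicator:

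adjusted effect = unadjusted effect + γ × (pC − pI)

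Here γ is the fitted coefficient of help, and pC and pI are the shares using help on the waiting list and in the intervention arm. Sample size does not enter. If sicker patients seek help, γ mixes the effect of help with the poorer mood of those who seek it, and it can be positive even when help works.

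**Illustration.** The documents give no rates of outside help, so every input except d = 0.50 (Sample size section) is assumed:

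- outcome in SD units, negative effects favouring the course;
- early mood M = −a × arm + R, with R standard normal, and final score = −a × arm + 0.7R + noise − e × help;
- logit P(help) = −0.8 + b × M + g × (waiting list), with b = 0.8 or 0 and g = 0.7 or 0;
- a = 0.5 or 0, and e = 0.3 (help works) or 0 (inert);
- 1,000,000 simulated patients per row.

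| Help depends on | Help works? | Effect without help | pC / pI | Unadjusted (ITT) | Adjusted | Adjusted − ITT | Adjusted − effect without help |
|---|---|---|---|---|---|---|---|
| mood | no | −0.50 | 0.33 / 0.26 | −0.500 | −0.464 | 0.036 | 0.036 |
| mood | yes | −0.50 | 0.33 / 0.26 | −0.474 | −0.460 | 0.014 | 0.040 |
| mood and arm | yes | −0.50 | 0.48 / 0.26 | −0.435 | −0.392 | 0.043 | 0.108 |
| mood and arm | no | 0 | 0.48 / 0.33 | 0.001 | 0.074 | 0.073 | 0.074 |
| mood and arm | yes | 0 | 0.48 / 0.33 | 0.042 | 0.070 | 0.028 | 0.070 |
| arm only | yes | −0.50 | 0.48 / 0.31 | −0.451 | −0.501 | −0.050 | −0.001 |
| neither | yes | −0.50 | 0.31 / 0.31 | −0.502 | −0.502 | 0.000 | −0.002 |

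Hand check of the third row: γ was 0.194, so the shift is 0.194 × (0.48 − 0.26) = 0.043, and −0.435 + 0.043 = −0.392. Help that truly lowers symptoms by 0.3 SD appears to raise them by 0.194 SD. A repeat with a different random seed and 4,000,000 patients per row agreed with every estimate to within 0.005.

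In the first five rows the adjusted estimate is 0.01 to 0.07 SD from the intention-to-treat estimate and 0.04 to 0.11 SD from the effect without outside help. In the third row, where help works as the contamination worry supposes, adjustment moves away from the effect it is meant to recover. In the sixth row it recovers that effect, because help there is unrelated to mood. In the last row nothing changes. By the formula, the shift changes sign if the intervention arm uses more outside help than controls.

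**Scale.** The planned 50 per condition gives a standard error of d of about √(2/50) = 0.20. A displacement of 0.04 to 0.11 is therefore 0.2 to 0.55 standard errors, or 8% to 22% of the planned effect of 0.50.

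**The case against.** The sentence is a conditional remark in the Discussion. It says what could be done and names no method; a method suited to post-randomisation treatment would not carry the same bias. An article may leave such detail to a fuller document. These limits stand, and they rule out three stronger readings that a reader might infer:

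- **That the primary estimate will be the corrected one.** The article does not say so, and the Statistical analyses section does not list outside care as a covariate.
- **That the plan contradicts its intention-to-treat commitment.** That section describes the principle as including all randomised participants however much of the course they complete. A supplementary adjusted analysis of the same patients is compatible with this. A conflict would arise only if the corrected figure replaced the main comparison.
- **That the corrected estimate is certainly biased or has no causal meaning.** The last two rows of the table show otherwise. Bias depends on how help relates to mood and arm, and the documents contain no data on either.

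It is also fair to say that the illustrated displacements are modest against the standard error and rest wholly on assumed inputs.

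The objection does not rescue the justification. The article presents the correction as its answer to contamination and makes it depend on power alone. That is a stated reason that does not hold, rather than a detail left out, and the rule on contacting the general practitioner makes the harmful case, help that follows mood, a likely one.

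**Conclusion.** The point holds in a limited form: ordinary covariate adjustment for outside help used after randomisation **can** bias the treatment effect, and adequate power offers no protection. In general it yields neither the intention-to-treat effect nor the effect without outside help.

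Size and direction cannot be derived from the documents. The range of 0.01 to 0.11 SD across both reference effects assumes that help depends on mood and that roughly a quarter to a half of patients use it. Where help did not depend on mood, no bias for the effect without outside help appeared. The point concerns the randomised glioma arms up to T2, before controls are offered the course. It merits a correction of the text but does not call the design into question.

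**What to change.** 1. State that the primary intention-to-treat comparison is not adjusted for care used after baseline.
2. Report outside psychological care from the TIC-P by arm at T1 and T2, so that readers can judge the extent of contamination.
3. If care is wanted as a covariate, use only the T0 TIC-P value. This assumes that the TIC-P is completed at T0; the article does not list instruments by visit.
4. Present any estimate of the effect without outside help as a labelled supplementary analysis, with its estimand defined and a method suited to post-randomisation treatment.
5. Remove the statement that adequate power makes the correction possible.

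The cost is wording only. Beyond the T0 assumption in item 3, no new data, visits or patients are needed, and the article describes the trial as still recruiting.

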## Abbreviations

BN20: EORTC brain cancer module; BSS: Beck scale for suicide ideation; CES-D: Center for epidemiological studies depression scale; CBT: Cognitive behavioral therapy; CIS: Checklist individual strength; CLL: Chronic lymphatic leukemia; EQ-5D: EuroQol; HRQOL: Health-related quality of life; MDS: Myelodysplastic syndrome; MM: Multiple myeloma; NHL: Non-Hodgkin lymphoma; PST: Problem-solving therapy; SF-36: -Form health survey; TIC-P: Trimbos/iMTA questionnaire for costs associated with psychiatric illness.
